#### Measurement of short chain fatty acids in stool

SCFAs (acetate, propionate, butyrate, formic acid, and isovaleric acid) will be isolated from 10 mg fecal aliquots, and measured using gas chromatography-mass spectrometry (GC/MS), according to the methods outlined in Moreau et al. [81] and Richardson et al. [82]. Briefly, in an aliquot of 10 mg fecal matter sample (with total protein content analysis by Bradford assay for normalization), add 2-ethylbutyrate internal standard in 0.5 ml water and 0.1 ml concentrated hydrochloric acid, shake 30 min with 1 ml MTBE including methylbutyrate internal standard. Decant MTBE phase, dry over sodium sulfate, derivatize with MTBSTFA at 80 °C for 30 min, inject 1 μl onto a 30 m 0.25 mm, 0.25 um DB5 duraguard column in a GC/MS with temperature gradient 50–290 °C, scanning 50–550 Da. Spiked recoveries in fecal matter range from 65 to 110% for formic acid to valerate. All short chain fatty acids had better than 7% within- and between-batch reproducibility and quantification limits < 10 pmol injected onto the column. Fecal samples will be centrally stored at -80°C at Loyola University Chicago after shipment from the field sites.

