### Bioinformatics data analysis

We will perform a Microbiome Wide Association Study (MWAS; [86]) to determine whether fecal microbial biomarkers are predictive of participant variables. Microbial 16S rRNA diversity will be summarized using Chao1 estimator and Shannon index, and the relative proportions of specific taxa. Significant relationships will be tested using generalized linear modeling. UniFrac distances (between-sample beta-diversity), microbial 16S rRNA diversity (alpha diversity, including evenness) will be correlated against the obesity and SCFA variables using multivariate methods such as principal coordinate analysis (PCoA), Analysis of the Composition of Microbiomes (ANCOM; [87]), and permutational multivariate analysis of variance (PERMANOVA). We will also employ correlative network modeling, including correction of multiple testing, to determine if the network associations (based on relative abundance correlation) differs with population, obesity and SCFA concentrations; such differences in node-level topological features of the network can help with interpreting ecological variability in the stability of each microbiome [88, 89]. We will characterize the modularity of these networks using a random walk approach and link these community structures to sample type via random forest modeling and multinomial logistic regression. Relative abundance of bacterial species will be characterized using sub-operational taxonomic unit level [85] . Based on DESeq2 results [90], logistic models will be fit using patient characteristics and SCFA concentrations as dependent variable and microbiome data as independent variables. Variable selection will be integrated to avoid over-fitting. Classification performance will be evaluated using ROC curve and the 0.632+ bootstrap method [91]. Random Forests will also be applied to determine whether the microbiome is predictive of participant variables [92].

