## Statistical considerations

### Overall approach and preliminary analysis

To ensure optimal model selection and protect against model overfitting, cross-validation techniques will be used to develop the models. The entire dataset will be randomly split into a training (60% of data) dataset and a test dataset (40%). Data will be divided using block randomization by site and gender to ensure equal contributions from the five sites. Models from each statistical approach will be fit using the training dataset and associations/predictions will be estimated on the validation set. Optimization of models and variable selection will involve a combination of stepwise selection and AIC criterion via 5-fold cross-validation [104]. The average validation error will also be used to assess model performance among the different statistical approaches and to choose the best approach for modeling this data. Univariate and bivariate summary statistics and distributional plots will be examined for all variables and appropriate transformations considered. Outliers will be identified using the “letter value” procedure which displays mild and severe outliers at the tails of the distribution [105, 106]. Associations between variables of interest will initially be explored with use of smooth scatter plots for continuous variables and cross-tabulations for discrete variables. Participant characteristics and baseline SCFAs values will be summarized by sex: overall and by site. Additionally, SCFAs concentrations will be examined by participant characteristics representing demographic and lifestyle factors that may be associated with exposure and outcomes of interest. Univariable comparisons will be examined via Pearson’s chi-square tests, Pearson’s correlation coefficients and Student’s t-tests, as appropriate. To account for potential differences in SCFAs levels by site, all modeling will adjust for site (in addition to age and gender) and, when feasible, modeling will be conducted within site to determine site-specific effects. All analyses will be performed using SAS version 9.4 (SAS Institutes, Cary, NC) and computing environment R (R Development Core Team, 2005).

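### A logistic/ROC step is named for SCFA concentrations, which are continuous and have no stated cut-point; secondarily, the plan does not say whether the DESeq2 step is repeated inside the 0.632+ bootstrap

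*Protocol article*

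**What the plan says.** Four statements in the section Bioinformatics data analysis bear on this point.

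- The modelling step: "Based on DESeq2 results [90], logistic models will be fit using patient characteristics and SCFA concentrations as dependent variable", with microbiome data as the independent variables.
- Selection: "Variable selection will be integrated to avoid over-fitting". What it is integrated into is not said.
- Assessment: "Classification performance will be evaluated using ROC curve and the 0.632+ bootstrap method".
- Elsewhere in the same section, diversity measures "will be correlated against the obesity and SCFA variables using multivariate methods", and relationships are to be tested by generalized linear models. No cut is mentioned for either.

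The section on measuring SCFAs in stool says that they are "measured using gas chromatography-mass spectrometry (GC/MS") and that "All short chain fatty acids had better than 7% within- and between-batch reproducibility".

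The section Overall approach and preliminary analysis adds a random split into 60% training and 40% test data, fitting on the training part for each statistical approach, and selection by stepwise methods and AIC with 5-fold cross-validation. It continues: "The average validation error will also be used to assess model performance among the different statistical approaches and to choose the best approach".

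**The concern.** **Main point.** A logistic model needs a binary or categorical outcome, and a ROC curve needs two classes. SCFA concentration is neither. The assay is described as precise, so the measurement gives no reason to coarsen it. The article names a model that does not fit the outcome it names, and the gap can be closed only by a cut that the plan does not state. Results of this step would then depend on the threshold, which could be chosen after seeing the data, and power would be lost. The plan expects that SCFA levels may differ by site, so whether the cut is pooled or within site would matter too.

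**Secondary point.** If features enter the logistic model because DESeq2 found them associated with the same outcome in the same participants, a bootstrap that starts from that shortlist cannot see the optimism created by the shortlisting. The AUC would then look better than the features deserve. This depends on where the screen sits, which the article leaves open.

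**Working it through.** The plan states no AUC, number of taxa, selection threshold or SCFA cut, so there is no figure of its own to reproduce.

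**1. Information kept when a continuous outcome is cut in two**

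Assume a normal outcome (for example log concentration) and small effects. If a share q lies above the cut c = z(1−q), the information kept relative to linear regression is φ(c)² / [q(1−q)].

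| Upper share q | c | φ(c) | Kept | Lost |
|---|---|---|---|---|
| 1/2 | 0 | 0.399 | 0.159/0.250 = 0.637 | 36.3% |
| 1/3 | 0.431 | 0.364 | 0.132/0.222 = 0.595 | 40.5% |
| 1/4 | 0.674 | 0.318 | 0.101/0.1875 = 0.539 | 46.1% |
| 1/10 | 1.282 | 0.175 | 0.0308/0.090 = 0.342 | 65.8% |

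The median split is the best two-class case (2/π = 0.637). In participants: the article gives 2506 recruited and about 65% retained, so 2506 × 0.65 ≈ 1629 before replacement recruits. A median split leaves the equivalent of 1629 × 0.637 ≈ 1037 of them for this step.

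If the step were read as an ordinal model with equal groups, the information kept is the mean of the squared group means. That is 0.793 for three groups (about 21% lost) and 0.861 for four (about 14% lost).

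**2. Does the position of the screen matter?**

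This was simulated with no feature related to a binary outcome, so the true AUC is 0.50. Assumptions: 500 or 2000 independent normal features; the top 20 or 50 kept by a univariate screen standing in for DESeq2; then logistic regression and a 0.632+ estimate of the AUC. Each setting used 4 data sets with 10 bootstraps each (Monte Carlo error about 0.01–0.02). The sample sizes are 2506; 1629; 0.6 × 1629 ≈ 977 (training share); and 325 (about one site, 1629/5).

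| n | Screen once, outside bootstrap | Screen repeated in each resample |
|---|---|---|
| 325 | 0.75–0.88 | 0.51–0.54 |
| 977 | 0.66–0.75 | 0.50–0.51 |
| 1629 | 0.63–0.71 | 0.50–0.51 |
| 2506 | 0.60–0.67 | 0.50–0.51 |

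When the screen used only the fitting data and the model was scored on separate held-out data, the AUC was 0.49–0.51.

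**3. How far the second table depends on the assumed rule**

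The simulation forces 20 or 50 noise features through whatever their significance. With 1,000 null features and a Benjamini-Hochberg threshold of 5% (200 data sets per n), nothing passed in 95%, 94% and 98% of data sets at n = 326, 977 and 1629, and never more than 3 features passed. The article states neither kind of rule.

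**The case against.** **On the SCFA outcome.** The wording may be loose. One sentence joins patient characteristics, some of which are binary, to SCFA concentrations, and a condensed article may leave the definition of classes to the full plan. The same section also provides generalized linear models and multivariate methods for SCFA variables, and the section Shotgun sequencing regresses on participant variables that include SCFAs. This limits the point. A reader might infer that the study as a whole throws away a third of its SCFA information. The documents do not support that, because any loss belongs to this one step and the 36% figure rests on an assumed median split. What remains is that the stated model does not match the stated outcome. That is a matter of what the text says, not of an omitted detail.

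**On the screen.** A stronger reading is tempting: that DESeq2 is run before and outside the bootstrap, so the plan will report an inflated AUC. The text does not say this. DESeq2 is named first, but the sentence on integrated selection can be taken to include it. The 60/40 split would also give an unbiased AUC if the screen stays in the training data. Against that, the article describes selection as stepwise and AIC-based without naming DESeq2, and the measure named for this step is the 0.632+ bootstrap rather than the test set. The point therefore stands only as a condition to be met.

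**On the validation error.** A reader might also infer that the 40% set is used to choose among approaches. The average validation error follows directly on the 5-fold cross-validation sentence and may well mean the folds. It is ambiguous, not shown to be a leak.

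**On importance.** The AUC is one of many analyses. The study's hypotheses do not name it as an endpoint, so it should not be treated as the main evidence.

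**Conclusion.** The main point holds. The plan assigns logistic models and classification performance to a continuous, precisely measured outcome without a cut-point. In this step a two-class cut would lose about 36% of the information at the median and more at any other binary cut, assuming a normal outcome and small effects. Ordered groups would lose less. A continuous-outcome model already falls within the generalized linear class that the plan names.

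The secondary point holds conditionally. If the DESeq2 screen is run once on all participants and left out of the resampling, the 0.632+ AUC will be optimistic. If it is repeated in each resample, or confined to the training data and tested once on held-out data, it will not. The simulated values show the direction and what is possible under an assumed top-20 or top-50 rule. They do not estimate this study's bias, because the feature numbers and the selection rule are not given.

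**What to change.** 1. In this step, model SCFA concentration as continuous: linear regression on the log scale or a gamma generalized linear model, reporting R2 and RMSE. Keep logistic models and ROC curves for binary variables such as obesity.
2. State that the DESeq2 screen and all later selection are repeated inside every bootstrap resample or fold, or are confined to the 60% training set.
3. State that approaches are compared by 5-fold cross-validation within the training set, and that the 40% test set is used once, for the chosen model.

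The cost is re-ordered analysis code, more computing time and possibly less favourable AUCs. No new data are needed.

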### Shotgun sequencing

We will perform shotgun metagenomic sequencing (20 million reads per sample) to characterize the functional metabolic pathways that may be enriched or depleted in different populations, obesity groupings, or SCFA concentrations. Libraries will be generated using 1 ng of input DNA with the Nextera XT protocol (Illumina), and sequenced on the Illumina HiSeq platform (150 bp × 2, 10 samples per lane, Insert size range = 300 bp to 1200 bp). Raw metagenome reads will be quality trimmed using the nesoni pipeline [93]. Phylogeny will be assigned to reads using MetaPhlAn [94]. Reads will be assembled using IDBA_UD [95], and population genomes will be binned using MetaBAT [96]. Single copy marker gene based copy number variation analysis [97] will be used to estimate completion and intra-species contamination in each genome. Reconstructed genomes will be annotated using RAST [98]. These genomes will be cross-referenced against the 16S rRNA amplicon results and comparative genomes between different strains will be regressed against participant variables (e.g. BMI, SCFAs, etc). Functional genes and metabolic pathways will be identified and statistically analyzed using HUMAN [99], and Hidden Markov Models [100] with DIAMOND [101] and the KEGG database [102]. Relative abundance will be assign to each KEGG Ortholog detected. Finally, we will apply Predicted Relative Metabolomic Turnover [103] to produce a predicted metabolite profile based on pathway reconstruction. The relative proportions of specific taxa, genes, or predicted metabolites associated with outcomes will be tested by regression analysis and generalized linear modeling. UniFrac distances (between-sample diversity) will be correlated with participant variables in principal coordinate analysis (PCoA), permutational multivariate analysis of variance (PERMANOVA).

### Data management

Loyola University Chicago is the coordinating center for the current study. All data forms, questionnaires and dietary recall instruments are scanned and, along with electronic Actical data files, sent via secure transfer to the data manager at the coordinating center. Scanned forms are coded and double data entered by experienced, trained study staff. A series of logic checks are then performed and, when outliers are encountered, discrepancies are followed up with staff at the appropriate field site.

## Statistical considerations

### Overall approach and preliminary analysis

To ensure optimal model selection and protect against model overfitting, cross-validation techniques will be used to develop the models. The entire dataset will be randomly split into a training (60% of data) dataset and a test dataset (40%). Data will be divided using block randomization by site and gender to ensure equal contributions from the five sites. Models from each statistical approach will be fit using the training dataset and associations/predictions will be estimated on the validation set. Optimization of models and variable selection will involve a combination of stepwise selection and AIC criterion via 5-fold cross-validation [104]. The average validation error will also be used to assess model performance among the different statistical approaches and to choose the best approach for modeling this data. Univariate and bivariate summary statistics and distributional plots will be examined for all variables and appropriate transformations considered. Outliers will be identified using the “letter value” procedure which displays mild and severe outliers at the tails of the distribution [105, 106]. Associations between variables of interest will initially be explored with use of smooth scatter plots for continuous variables and cross-tabulations for discrete variables. Participant characteristics and baseline SCFAs values will be summarized by sex: overall and by site. Additionally, SCFAs concentrations will be examined by participant characteristics representing demographic and lifestyle factors that may be associated with exposure and outcomes of interest. Univariable comparisons will be examined via Pearson’s chi-square tests, Pearson’s correlation coefficients and Student’s t-tests, as appropriate. To account for potential differences in SCFAs levels by site, all modeling will adjust for site (in addition to age and gender) and, when feasible, modeling will be conducted within site to determine site-specific effects. All analyses will be performed using SAS version 9.4 (SAS Institutes, Cary, NC) and computing environment R (R Development Core Team, 2005).

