**Methods:**

The parent study; Modeling the Epidemiologic Transition Study (METS) is a well-established and ongoing prospective cohort study designed to assess the association between body composition, physical activity, and relative weight, weight gain and cardiometabolic disease risk in five diverse population-based samples in 2500 people of African descent. The cohort has been prospectively followed since 2009. Annual measures of obesity risk factors, including body composition, objectively measured physical activity and dietary intake, components which vary across the spectrum of social and economic development. In our new study; METS-Microbiome, in addition to continuing yearly measures of obesity risk, we will also measure gut microbiota and stool SCFAs in all contactable participants, and follow participants for a further 3 years, thus providing one of the largest gut microbiota population-based studies to date.

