Insoluble Fiber (g/day)	18.9 ± 7.5	5.8 ± 2.9	11.6 ± 6.1	9.6 ± 5.1	9.5 ± 5.38
Obesity (%)	9.8	32.1	27.6	26.4	52.4
Diabetes (%)	1.0	2.4	0.2	3.4	9.6

^a^Sites are presented according to their level of Epidemiologic Transition, using Human Development Index rankings. Diabetes, random glucose > 140 mg/dL or currently taking diabetes medication

For the new study; METS-Microbiome (R01-DK111848), data and biological samples collected during subsequent years of follow-up examinations will be utilized for year 8–10 follow up (2018–2021). As indicated, a total of 2506 participants were recruited at baseline (2010–2011). At present, across all sites, we have approximately 65% retention of the original cohort. Recruitment and replacement of participants lost to follow-up has begun in the sites.

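### Associations of exposures named in advance appear to be estimated on a 40% hold-out, with no full-sample fit stated; read literally, their standard errors are about 1.58 times those of a full-sample fit

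*Protocol article*

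**What the plan says.** All of this stands in the protocol article, Statistical considerations, Overall approach and preliminary analysis, unless another section is named.

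- Purpose: "To ensure optimal model selection and protect against model overfitting, cross-validation techniques will be used to develop the models".
- Split: "The entire dataset will be randomly split into a training (60% of data) dataset and a test dataset (40" (the last figure is the test percentage). It is stratified: "Data will be divided using block randomization by site and gender to ensure equal contributions from the five sites".
- Use of the two parts: "Models from each statistical approach will be fit using the training dataset and associations/predictions will be estimated on the validation set".
- Selection: "Optimization of models and variable selection will involve a combination of stepwise selection and AIC criterion via 5-fold cross-validation".
- All models adjust for site, age and gender, and models within site are planned where feasible.

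The two parts of the split are called training and test. The term *validation set* appears without definition, and a validation error is mentioned just after the 5-fold cross-validation. No refit of a final model on all participants, repeated splitting or cross-fitting is described.

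**The concern.** A hold-out serves two purposes: judging prediction honestly, and re-estimating effects of features that were chosen by looking at the data. Neither applies to an exposure named before the data are seen and entered in a model whose covariates are also fixed beforehand. Nothing is selected there, so an estimate from part of the cohort is simply less precise than one from the whole.

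The sentence on the two parts names associations alongside predictions, so it sets a rule for effect estimates as well as for predictive performance. The three hypotheses are largely about association: shared factors across populations, cross-sectional factors that predict later change, and shared versus local relationships. The third leans on site-specific estimates, which have the smallest samples to begin with. The Abstract (Methods) presents the study as "thus providing one of the largest gut microbiota population-based studies to date". That statement is not an error, but under the literal rule the size would not reach these modelled estimates.

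**Working it through.** **Inputs from the article.** Split 60/40, stratified by site and gender. Cohort: "a total of 2506 participants were recruited at baseline (2010–2011"), with about 500 per site (Design and settings, Table 1). Retention is about 65%, with replacement under way and no final number given (Design and settings).

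**Assumptions.** The article gives no alpha, power or effect size for these analyses. I assume two-sided 5%, 80% power, no multiplicity correction, a simple correlation as the measure of association, and a split by participant. For the lower within-site figure I assume that 65% retention is equal across sites. There is no figure in the plan to reproduce.

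**Step 1: standard error.** SE is proportional to 1/sqrt(n), so the ratio to the same model fitted to all participants depends only on the fraction used.

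- Estimate from the 40% test part: sqrt(1/0.40) = 1.58.
- Coefficient from the 60% training fit: sqrt(1/0.60) = 1.29.

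**Step 2: sample sizes.** 0.40 × 2506 = 1002. At 65% retention, 0.65 × 2506 = 1629 and 0.40 × 1629 = 652. Within site, 0.40 × 500 = 200. At 65%, 1629/5 = 326 and 0.40 × 326 = 130.

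**Step 3: smallest detectable correlation**, by Fisher z: r = tanh((1.960 + 0.842)/sqrt(n − 3)).

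| Setting | n, all | r, all | n, 40% part | r, 40% part |
|---|---|---|---|---|
| Pooled, baseline enrolment | 2506 | 0.056 | 1002 | 0.088 |
| Pooled, 65% retained | 1629 | 0.069 | 652 | 0.110 |
| One site, baseline enrolment | 500 | 0.125 | 200 | 0.197 |
| One site, 65% retained | 326 | 0.155 | 130 | 0.244 |

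If coefficients come from the 60% fit, the pooled values are 0.072 (n = 1504) and 0.090 (n = 977).

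**Step 4: power.** An effect with 80% power on all participants has power Φ(2.802 × sqrt(0.40) − 1.960) = Φ(−0.188), about 43%, on the 40% part.

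**Step 5: where the comparison does not apply.** A null simulation (assumed N = 1000, 30 independent candidate features, strongest one selected, 1,500 repetitions) compared two procedures at nominal 5%. Selecting and testing on the same full data gave 79% false positives, close to 1 − 0.95^30 = 0.785. Selecting on 60% and testing on the other 40% gave 5.4%. For data-selected features the naive full-sample standard error is therefore not a valid yardstick, and the factor 1.58 must not be read as waste.

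**The case against.** **A stronger reading is tempting.** Because the split covers the whole dataset, a reader might infer that 60% of the cohort never contributes to any effect estimate and that every standard error in the study is inflated. The article does not support this, for three reasons.

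- The same sentence fits the models on the training part, and fitting yields coefficients. The 60% may supply the estimates, with the hold-out checking them. With *validation set* undefined, it could even mean the folds of the 5-fold cross-validation.
- Several association analyses are not tied to the split: the univariable chi-square, correlation and t-tests in the same section, the 16S tests in Bioinformatics data analysis, and the metagenomic regressions in Shotgun sequencing.
- After stepwise selection, part of the larger standard error is the price of valid inference, as Step 5 shows. A single split-sample confirmation is a defensible choice in a microbiome-wide search.

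**It can also be said that the plan has no selection-free model.** Only site, age and gender are always included, Covariates of interest lists many more candidates, and stepwise selection is described generally. This is correct. The saving is available only if a covariate set is fixed beforehand, so the remedy must say so.

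**Finally, the article is condensed**, and a fuller document may describe a full-sample fit. That limits how firmly one can say what will be done. It does not change what the printed sentence prescribes: associations estimated on a held-out part.

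These objections narrow the point to modelled associations of pre-named exposures. They do not remove it: on the readings above, such an estimate uses 40% or 60% of participants, and the text does not say which.

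**Conclusion.** The point holds for associations of exposures named in advance when they are estimated from the developed models. Read literally, their standard errors are 1.58 times those of the same pre-specified model fitted to all participants, or 1.29 times if the 60% fit supplies the coefficients. These ratios do not depend on the final sample size. The detectable correlations do, and they rest on the assumed alpha and power. Within site, the loss is from 0.125 to about 0.20 at baseline enrolment and from 0.155 to about 0.24 at 65% retention. The final number after replacement is not given, so these two cases serve as an illustrative range.

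The point does not extend to the univariable, 16S or metagenomic tests described without reference to the split, nor to features selected from the data.

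**What to change.** In Overall approach and preliminary analysis:

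1. State that associations of pre-named exposures (acetate, propionate, butyrate, alpha diversity) are estimated on all participants. Use a covariate set fixed in advance (site, age, gender and chosen variables from Covariates of interest) and no stepwise selection.
2. Keep the 60/40 split for prediction performance and for confirming data-selected features.
3. State that the validation set means the 40% test set.

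Repeated splitting or cross-fitting for selected features is optional. It uses more of the data and depends less on one random split. However, fold estimates are correlated, there is no longer a single untouched hold-out, and a rule is needed for folds that select different features.

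The cost is mainly wording. The exposures and covariates must be settled before analysis, and the pre-named associations will have no separate hold-out confirmation.
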